## Abstract

**Introduction:**

Acute kidney injury (AKI) affects ~30% of hospitalized neonates. Critical to advancing our understanding of neonatal AKI is collaborative research among neonatologists and nephrologists. The Neonatal Kidney Collaborative (NKC) is an international, multidisciplinary group dedicated to investigating neonatal AKI. The AWAKEN study (Assessment of Worldwide Acute Kidney injury Epidemiology in Neonates) was designed to describe the epidemiology of neonatal AKI, validate the definition of neonatal AKI, identify primary risk factors for neonatal AKI, and investigate the contribution of fluid management to AKI events and short-term outcomes.

**Methods and analysis:**

The NKC was established with at least one pediatric nephrologist and neonatologist from 24 institutions in 4 countries (USA, Canada, Australia, and India). A Steering Committee and four subcommittees were created. The database subcommittee oversaw the development of the web-based database (MediData Rave™) that captured all NICU admissions from 1/1/14 to 3/31/14. Inclusion and exclusion criteria were applied to eliminate neonates with a low likelihood of AKI. Data collection included: (1) baseline demographic information; (2) daily physiologic parameters and care received during the first week of life; (3) weekly “snapshots”; (4) discharge information including growth parameters, final diagnoses, discharge medications, and need for renal replacement therapy; and (5) all serum creatinine values.

**Ethics and dissemination:**

AWAKEN was proposed as human subjects research. The study design allowed for a waiver of informed consent/parental permission. NKC investigators will disseminate data through peer-reviewed publications and educational conferences.

**Discussion:**

The purpose of this publication is to describe the formation of the NKC, the establishment of the AWAKEN cohort and database, future directions, and a few “lessons learned.” The AWAKEN database includes ~325 unique variables and >4 million discrete data points. AWAKEN will be the largest, most inclusive neonatal AKI study to date. In addition to validating the neonatal AKI definition and identifying risk factors for AKI, this study will uncover variations in practice patterns related to fluid provision, renal function monitoring, and involvement of pediatric nephrologists during hospitalization. The AWAKEN study will position the NKC to achieve the long-term goal of improving the lives, health, and well-being of newborns at risk for kidney disease.

## Introduction

Over the last decade, the nephrology and critical care communities have repeatedly shown that acute kidney injury (AKI) in children (1, 2) and adults (3–7) portends poor short-term and long-term outcomes independent of severity of illness. The available short-term outcome data in neonates are similar: neonates with AKI have increased rates of mortality and longer hospital stays as compared to those without AKI (Table 1) (8–14). The prevalence of AKI reaches ~30% in neonates admitted to a tertiary level neonatal intensive care unit (NICU) (8–13, 14). However, prevalence estimates and data on short-term outcomes are solely derived from small retrospective, single-center studies. Moreover, little is known about the long-term consequences of neonatal AKI (15). Many significant questions, including how to best define, risk factors for, incidence of, association with other co-morbidities, and the short-term and long-term outcomes after AKI remain unanswered.

**Table 1 T1:** **Neonatal AKI prevalence and mortality rates**.

	Prevalence (%)	Mortality AKI vs. no AKI (%)	Reference
VLBW^a^	18	55 vs. 5	(8, 14)
	40	14 vs. 4	
ELBW^b^	13	70 vs. 22	(9)
Sick near term/term	18	22 vs. 0	(10)
Sepsis	26	70 vs. 25	(13)
Asphyxiated	38	14 vs. 2	(12)
ECMO	71	73 vs. 20^c^	(11)

*^a^Very low birth weight (VLBW) infants <1500 g*.

*^b^Extremely low birth weight (ELBW) infants <1000 g*.

*^c^Extracorporeal membrane oxygenation (ECMO)*.

Critical to advancing the field of neonatal AKI is collaborative research among neonatologists and pediatric nephrologists. To foster this partnership, the National Institutes of Health (NIH) sponsored a multidisciplinary workshop on neonatal AKI in April 2013 (16, 17). Soon after, the Neonatal Kidney Collaborative (NKC) was formed to address the critical gaps in knowledge highlighted at the workshop. The NKC is an international working group composed of neonatologists and pediatric nephrologists committed to advancing the field of neonatal AKI research. The first mission of the NKC was to develop the infrastructure to function. The second mission of the NKC was the development of the AWAKEN study (Assessment of Worldwide Acute Kidney injury Epidemiology in Neonates), a large, retrospective cohort study designed with the following aims: (1) determine if the Kidney Disease: Improving Global Outcomes (KDIGO) AKI definition, adapted to neonates, is independently associated with mortality, length of stay, and discharge serum creatinine (sCr), (2) define the risk factors associated with neonatal AKI, (3) determine how fluid balance during the first few weeks of life relates to biochemical data and clinical outcomes, and (4) assess the performance of different definitions of AKI in neonates.

Assessment of Worldwide Acute Kidney injury Epidemiology in Neonates is the largest and most inclusive neonatal AKI study to date. Evaluation of these important questions will improve care and stimulate new research questions that will drive this field for many years. Collaborations will foster strong relationships between neonatologists and pediatric nephrologists within and across centers. The infrastructure created to perform the AWAKEN study will position this group to conduct additional clinically relevant, hypothesis-driven studies aimed at improving the lives, health and well-being of patients at risk for kidney disease as the result of events during the newborn period. Here, we describe the formation of the NKC, the establishment of the AWAKEN cohort and database, future directions, and a few “lessons learned” in the process.

### Development of the Neonatal Kidney Collaborative

The NKC is a voluntary, non-funded group made up of pediatric centers who agreed to ensure: (1) the participation of both a neonatologist and pediatric nephrologist from their institution and (2) local IRB approval. The NKC membership evolved from professional relationships developed through previous clinical and research interactions including the 2013 NIH workshop “Neonatal AKI.” A current roster of participating institutions is included in Table 2.

**Table 2 T2:** **Participating institutions**.

Institution	Location (city, state, country)	Enrolled in AWAKEN (*n*)	% inborn	Creatinine assay
Canberra Hospital	Canberra, ACT, Australia	37	76	Jaffe
Children’s Hospital Colorado	Denver, CO, USA	68	7	Enzymatic
Children’s Hospital at Montefiore	Bronx, NY, USA	91	96	Enzymatic
Children’s National Medical Center	Washington, DC, USA	86	1	Enzymatic
Cincinnati Children’s Hospital Medical Center	Cincinnati, OH, USA	81	9	Enzymatic
Maimonides Medical Center	Brooklyn, NY, USA	53	94	Enzymatic
Medanta –The Medicity Hospital	Gurgaon Haryana, India	58	22	Jaffe
MetroHealth Medical Center	Cleveland, OH, USA	69	100	Jaffe
Montreal Children’s Hospital/McGill University	Montreal, Quebec, Canada	67	0	Jaffe
Nationwide Children’s Hospital	Columbus, OH, USA	81	0	Enzymatic
Stony Brook Children’s Hospital	Stony Brook, NY, USA	78	90	Enzymatic
Texas Children’s Hospital	Houston, TX, USA	106	67	Enzymatic
Tufts University	Boston, MA, USA	87	67	Enzymatic
University of Alabama at Birmingham	Birmingham, AL, USA	59	63	Jaffe
University of British Columbia and Children’s and Women’s Health Center of British Columbia Branch	Vancouver, BC, Canada	104	63	Enzymatic
University of Iowa	Iowa City, IO, USA	121	58	Enzymatic
University of Kentucky	Lexington, KY, USA	116	54	Enzymatic
University of Miami	Miami, FL, USA	192	90	Enzymatic
University of Michigan	Ann Arbor, MI, USA	93	72	Jaffe
University of New Mexico	Albuquerque, NM, USA	81	81	Enzymatic
University of Rochester	Rochester, NY, USA	151	77	Enzymatic
University of Virginia	Charlottesville, VA, USA	101	66	Jaffe
University of Washington	Seattle, WA, USA	63	98	Both
Washington University in St. Louis	St. Louis, MO, USA	120	1	Enzymatic

The NKC infrastructure consists of the Steering Committee overseen by the Director and the co-chairpersons of the four subcommittees (Figure 1). Each subcommittee (Protocol Committee, Manuscript Committee, Database Committee, and Ancillary Studies Committee) is co-chaired by a pediatric nephrologist and a neonatologist, thereby assuring that the clinical expertise of both specialties is represented.

**Figure 1 F1:**
[figure not shown]
**The Steering committee is composed of the director and the co-chairs of each of the sub-committees**. The Protocol Committee was tasked to provide oversight and critique of the protocols submitted to the committee, both for the initial retrospective study (AWAKEN) and any future studies. It will also be charged with creating and submitting protocols to funding agencies and Institutional Review Boards. Other responsibilities include establishing rules for Primary Investigator designation and a system for group involvement for the establishment of future protocols. The Database Committee was charged with the development of the database, including the Manual of Procedures and Case Report Forms. Input was solicited from the NKC membership as to the data needed to answer the specific questions of interest for the AWAKEN study. These suggestions were collated and presented to the Steering Committee for final review. The myriad of data potentially available and the number of questions to be answered had the potential for an unwieldy and overwhelming amount of information. Data points that were included were thoroughly vetted by both nephrologists and neonatologists to balance the time of data collection with quality of the data elements. Once agreement was reached, in concert with the Data Management Center at Cincinnati Children’s Hospital Medical Center, electronic data forms were developed, tested, and finalized. The Manuscript Committee is responsible for initiating and developing abstracts for national and international meetings and manuscripts for submission to peer-reviewed journals. This committee will also review these abstracts and manuscripts prior to submission and provide the authors suggestions, as well as determine their suitability. The Ancillary Studies Committee will be responsible for developing rules on requesting use of data for ancillary studies and in developing these ideas into abstracts and manuscripts.

### The AWAKEN Study

While research interest in neonatal AKI has increased greatly over the last 5 years, advances in clinical recognition, diagnosis, and supportive care for AKI in this population have lagged behind advances seen for adult and older pediatric patient groups (18). One major limitation to moving this field forward has been the lack of a standardized and validated definition of AKI in neonates similar to those used in adult and pediatric patients [e.g., risk, injury, failure, loss and end-stage RIFLE (19), KDIGO (20)]. The lack of a common definition has led to an inability to recognize AKI early and consistently across patients as well as an inability to pool or compare data across studies. In addition, the unique renal physiology of preterm and term infants creates challenges for the use of serum creatinine (sCr) as an AKI biomarker in these patients. Neonatal SCr initially reflects maternal values and then decreases over subsequent weeks after birth at different rates depending on gestational age. In addition, “normal” serum creatinine levels vary widely based on weight and gestational age. Before 2005, the majority of neonatal AKI studies used an arbitrary definition of AKI defined by a serum creatinine concentration (SCr) ≥1.5 mg/dl. In 2012, Jetton and Askenazi (21) proposed a standardized neonatal AKI definition based on the KDIGO definition for adults and children (Table 3) that identifies three levels of AKI severity based on graded changes in both serum creatinine and urine output. This and similar definitions have been utilized successfully in select neonatal patient populations (8, 10–12, 14, 22, 23). Consensus at the NIH neonatal AKI workshop was that this definition, despite its limitations, was currently the most appropriate definition to adopt and validate ([name], personal communication). The group stressed the need to conduct large multi-center studies to test the performance of this definition against clinically relevant outcomes and further refine the definition based on data generated from these large cohorts. Thus, the AWAKEN study was designed to fulfill this charge and determine the extent to which the definition of AKI is associated with the short-term outcomes of mortality, length of stay, and discharge sCr. Although the association of neonatal AKI with longer term outcomes is beyond the scope of the AWAKEN study, the data generated will provide the foundation for prospective follow-up studies and the groundwork for prospective studies of at-risk populations.

**Table 3 T3:** **Neonatal acute kidney injury KDIGO classification (21)**.

Stage	Serum creatinine	Urine output
0	No change in sCr *or* rise <0.3 mg/dl	> 1 ml/kg/h
1	sCr rise ≥0.3 mg/dl within 48 h or sCr rise ≥1.5–1.9× reference sCr^a^ within 7 days	> 0.5 ml/kg/h and ≤ 1 ml/kg/h
2	sCr rise ≥2–2.9× reference sCr^a^	>0.3 ml/kg/h and ≤ 0.5 ml/kg/h
3	sCr rise ≥3× reference SCr^a^ or sCr ≥2.5 mg/dl^b^ or receipt of dialysis	≤ 0.3 ml/kg/h

Differences between the proposed neonatal AKI definition and KDIGO include:

*^a^Reference sCr will be defined as the lowest previous sCr value*.

*^b^sCr value of 2.5 mg/dl represents less than 10 ml/min/1.73m^2^*.

Similarly, fluid overload has been identified as a major risk factor for morbidity and mortality in adult and pediatric patients with AKI (24, 25), but has not been fully examined in the neonatal population. As with the study of sCr in this group, the unique physiology of neonates, especially premature and low-birth weight infants, creates challenges for applying concepts developed in older patients to this special group. In the first few days after birth, healthy term infants will lose around 7% of their weight. Depending on the amount of fluid provision, ambient temperature and humidity, gestational age, and kidney function, infants admitted to the NICU will have different amounts of weight losses due to changes in fluid balance over the first weeks of life (26).

Appropriate fluid balance is critical to the care of newborns. In premature infants, mild fluid weight losses over the first week of life are desirable as high fluid intake can be associated with patent ductus arteriosus, bronchopulmonary dysplasia, cardiac failure, necrotizing enterocolitis, and intraventricular hemorrhage (27). Alternatively, inadequate fluid provision may cause hemodynamic dysfunction potentially resulting in AKI. However, in the extremely low-birth weight (ELBW) and extremely low gestational age neonate (ELGAN), fluid balance cannot be calculated in the same way as in older, larger neonates, or pediatric patients [e.g., using documented intake and output volumes to calculate fluid overload or fluid deficits (28)]. Transepidermal fluid losses (TEFL) in the first week will vary considerably as a function of ambient humidity and are impossible to measure in clinical practice. Although at birth TEFL in healthy full-term neonates is similar to that in older children and adults (4–8 g/m^2^/h), it is estimated to be 75 g/m^2^/h in neonates born at 23 weeks’ gestation (29). Humidified incubators simplify the management of fluids in these infants and help prevent extremes of electrolyte abnormalities. An important objective in AWAKEN will be to determine if variations in body weight are an adequate surrogate for fluid balance in this population rather than the reliance on recorded intake and output for calculation of fluid overload as is used in older patients. We also seek to determine whether fluid overload functions as a sign of kidney injury and increases the risk of morbidity and mortality as has been shown in older patient groups.

The primary hypothesis of AWAKEN is that neonatal AKI is common and associated with increased mortality, longer length of NICU stay and higher discharge serum creatinine, even after controlling for severity of illness, interventions and demographics. The two secondary hypotheses of AWAKEN include (1) maternal and infant risk factors can predict AKI and (2) fluid balance is associated with clinical outcomes (Table 4). Ultimately, the NKC will be positioned to test and validate the proposed neonatal AKI definition and compare it with other AKI definitions to determine which definition is the most accurate. We anticipate that the AWAKEN study can validate these hypotheses because of the large sample size and rich data set. This multicenter study will also uncover variations in practice patterns among NICUs in relation to fluid provision, renal function monitoring, bedside identification of AKI and AKI risk factors, and the involvement of pediatric nephrologists during inpatient hospitalization. Moreover, AWAKEN will provide important information regarding critical time and data points necessary to build a meaningful prospective study in the future.

**Table 4 T4:** **Primary hypotheses of AWAKEN**.

*Hypothesis #1*: Neonatal AKI is associated with short-term risk, even when adjusted for gestational age at birth, birthweight, 5 min Apgar score, congenital renal anomalies, and severity of illness score	Survival of infants to discharge or 120 days of age (or to 36 weeks’ postmenstrual age in infants born preterm) is less likely in babies with the diagnosis of AKI
	Length of stay is longer in infants with neonatal AKI
	Discharge serum creatinine is higher in infants with neonatal AKI
*Hypothesis #2*: Maternal and infant risk factors predict AKI	
*Hypothesis #3*: Fluid balance during the first week after birth is associated with short-term risk	Survival of infants to discharge or 120 days of age (or to 36 weeks’ postmenstrual age in infants born preterm) is less likely in babies with excessive fluid intake compared to output
	Changes in weight are a better indication of fluid balance, especially in the preterm population, than difference between fluid intake and measured output
	Length of stay is longer in infants with neonatal AKI
	Pulmonary outcomes, as measured by time to extubation and development of bronchopulmonary dysplasia, are worse in infants with evidence of fluid overload
	Discharge serum creatinine is higher in infants with fluid overload

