## Methods and Analysis

### Design

Assessment of Worldwide Acute Kidney injury Epidemiology in Neonates is a multi-center, international, retrospective cohort study. All neonates who fulfilled the inclusion and exclusion criteria at each of the 24 participating centers from January 1, 2014 until March 31, 2014 were enrolled (Figure 2). Detailed data collection continued until one of the following endpoints was reached: discharge to home, transfer to another facility or out of the NICU for escalating or convalescent care, death or 120 days of age. Limited information was collected between 120 days and final disposition. The study was registered at ClinicalTrials.gov (https://clinicaltrials.gov/ct2/show/NCT02443389?term=kidney+awaken&rank=1).

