### Variable Collection

The AWAKEN study was designed to acquire information that is most likely related to kidney function and kidney injury in critically ill neonates. All sCr values during the study period were recorded. Data collection was otherwise organized into five components. Case report forms (CRF) and manual of operations are included in Supplementary Materials, Data Sheet 2.

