### Analyses

Data management and statistical analysis will be executed at the University of Alabama at Birmingham using SAS software v9.4 (SAS Institute, Cary, NC, USA). Analysis of data will be performed independently for each specific aim. Descriptive statistics will be used to describe the populations of NICU patients overall, with and without AKI. Data will be analyzed to compare the different definitions of neonatal AKI.

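### Hypothesis #1 contrasts infants with and without AKI but ties AKI to no point in time, so stay would look longer with AKI under the null, while mortality is biased the other way

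*Protocol article*

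**What the plan says.** The primary hypothesis (The AWAKEN Study) is that neonatal AKI is "associated with increased mortality, longer length of NICU stay and higher discharge serum creatinine". Table 4, Hypothesis #1, words two of its parts as group contrasts: survival "is less likely in babies with the diagnosis of AKI", and "Length of stay is longer in infants with neonatal AKI". The association is to hold "even when adjusted for gestational age at birth, birthweight, 5 min Apgar score, congenital renal anomalies, and severity of illness score".

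Table 3 stages AKI by creatinine and urine output and gives no age by which AKI must arise. Its footnote a reads "Reference sCr will be defined as the lowest previous sCr value". Under Variable Collection, "All sCr values during the study period were recorded". Under Design, detailed collection ends at "discharge to home, transfer to another facility or out of the NICU for escalating or convalescent care, death or 120 days of age".

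Table 4 counts survival to discharge or 120 days of age, or to 36 weeks' postmenstrual age for preterm infants. The Analyses section says "Descriptive statistics will be used to describe the populations of NICU patients overall, with and without AKI" and that each aim is analysed separately in SAS. It names no regression or time-to-event model.

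**The concern.** AKI status builds up over the stay, and the stay is itself an outcome. An infant who leaves on day 10 has ten days in which to qualify; one who leaves on day 60 has sixty. Sorting infants by whether they ever qualified puts long-stay infants into the AKI group whether or not AKI lengthens the stay. The adjusters in Table 4 describe the infant at or near birth and the severity of illness. None of them is time at risk.

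For mortality the direction reverses. An infant who develops AKI on day 20 had to be alive on day 20, and an infant who dies early has little time to qualify. This makes AKI look protective and works against the survival hypothesis.

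For preterm infants there is a further problem of order. The survival horizon may be 36 weeks' postmenstrual age, while creatinine is collected until discharge or day 120. An infant born at 28 weeks reaches that horizon at (36 − 28) × 7 = 56 days, so AKI first diagnosed between days 56 and 120 would come after the outcome it is meant to explain.

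Aim 1 asks whether the AKI definition is independently associated with these outcomes. A stay difference that appears under the null cannot support that.

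**Working it through.** The article states no effect size, power or model for Hypothesis #1, so there is no figure to reproduce. The check asks what a with-versus-without contrast shows when AKI has no effect.

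**Inputs from the article.** AKI prevalence of about 30% (Introduction), with 13% to 71% across the subgroups of Table 1; follow-up to 120 days; ends of follow-up as in Design.

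**Inputs assumed, because the article gives none.** The distributions of stay, AKI onset and death. Two sets were used.

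**Mechanism.** With daily AKI hazard h(t) independent of stay, the probability of being labelled AKI by the end of a stay T is 1 − exp(−H(T)), where H(T) is the hazard summed to T. Take 0.03 per day in week 1 and 0.004 after:
- T = 10: H = 0.21 + 0.012 = 0.222, probability 19.9%.
- T = 60: H = 0.21 + 0.212 = 0.422, probability 34.4%.

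The label depends on stay although AKI has no effect on stay.

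**Model A, crude.** Potential stay lognormal (median 20 days, log-SD 0.9), mortality about 5%, 30% ever AKI, 2,000,000 infants per scenario. Ranges cover an early-death pattern and a constant death hazard.

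| Week-1 AKI hazard relative to later | Median stay, AKI (days) | Median stay, no AKI (days) | False excess (days) |
|---|---|---|---|
| 1 | 34.1–34.9 | 14.9–15.3 | about 19–20 |
| 5 | 26.4–26.8 | 16.6–16.9 | about 10 |
| 20 | 22.0–22.1 | 17.8–18.0 | about 4 |
| 100 | 20.4–20.5 | 18.4–18.6 | about 2 |

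At the 5-fold ratio with early deaths, prevalence of 18% or 40% gives 27.8 vs 17.6 and 25.8 vs 15.7 days. Adding 15% transfers gives 25.0 vs 15.9.

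**Model A, mortality under the null.** With early deaths, AKI vs no AKI runs from 1.5% vs 5.1% (ratio 1) to 3.2% vs 4.3% (ratio 100). With a constant death hazard it is 4.8% vs 5.4%. AKI looks protective in every case.

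**Model B, with adjustment.** Stay = 2 + Weibull (shape 1.2, mean 30 days), capped at 120. The score behind stay is s = √R²·z + √(1 − R²)·e, where z is a baseline factor such as gestational age and R² its share of the variance. The adjusted difference is averaged over strata of z.

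| Daily hazard, week 1 / later | Share of AKI in week 1 | Mean stay AKI vs no AKI, crude (days) | Adjusted excess, R² = 50% | R² = 70% | R² = 80% |
|---|---|---|---|---|---|
| 0.04 / 0.002 | 87% | 35.6 vs 30.5 | 2.6 | 1.5 | 1.0 |
| 0.03 / 0.004 | 71% | 38.6 vs 29.4 | 4.9 | 3.0 | 2.0 |
| 0.02 / 0.006 | 53% | 42.2 vs 28.5 | 7.4 | 4.6 | 3.1 |

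The crude false excess is 5 to 14 days and the adjusted one about 1 to 7 days. As a ratio of stays, a separate check gave 1.12–1.30 at 50% and 1.05–1.12 at 80%.

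**After tying AKI to time.** With a day-7 landmark (AKI by day 7, infants still followed on day 7), the false difference disappears. In model A, median stay is about 22.3 vs 22.3 days, and deaths are about 2.1% vs 2.1% (early deaths) or 4.6–4.7% vs 4.6% (constant hazard). In model B, mean stay is 34.8 vs 34.9 days.

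**The case against.** The strongest objection is that the article states a hypothesis and not a method. An association of AKI with mortality and stay could be tested with a time-dependent Cox or multistate model, and a plan that is not shown may do so. This stands in part. A reader might infer that a fixed AKI covariate is planned; the article does not say that. What it does fix is an open-ended AKI window, a with-versus-without contrast and an adjustment list without time at risk. Hypothesis #3 in the same table ties its exposure to the first week after birth, whereas the primary hypothesis has no such anchor.

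Second, crude differences overstate the problem, because gestational age and birthweight plausibly explain much of the stay. This stands, and the adjusted range should be read alongside the crude one. Adjustment shrinks the bias without removing it.

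Third, the article regards the first 2 weeks as the critical at-risk time. If nearly all AKI arises in week 1, the crude excess is only about 2 days. This also stands.

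Fourth, deaths before 48 h are excluded, and the mortality bias is conservative for the stated hypothesis. Both are true, but later deaths remain, and a conservative bias still distorts the estimate.

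Some stronger readings are not supported:
- A longer stay does not create AKI. It gives more time for AKI to occur or be found.
- Nothing says that infants transferred for escalating care are counted as alive. Discharge Data records that status separately, and the survival rule for it is not stated.
- The 120-day limit does not by itself truncate stay, because the date of final disposition is collected for longer stays.

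**Conclusion.** The point holds in this form: taken literally, the primary contrast produces a longer stay with AKI when AKI has no effect, and it pulls the mortality contrast towards apparent protection. For preterm infants the exposure may also follow the survival horizon.

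The direction was the same in every scenario. The size rests on assumed stay, onset and death distributions: about 2 to 20 days crude over both models. The adjusted figure of about 1 to 7 days comes from model B only, with a baseline factor explaining 50% to 80% of stay variance. Both depend mainly on how early AKI arises.

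The conclusion is that the wording leaves a material bias open, not that the trial's analysis is known to be biased. It should be settled before the stay and mortality results are used to validate the AKI definition.

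**What to change.** State in the analysis plan:

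1. AKI is a time-dependent exposure: an infant is unexposed until the first value that meets Table 3 and exposed from then on. AKI first diagnosed after the survival horizon then cannot count towards that endpoint.
2. A day-7 landmark is a sensitivity analysis: AKI by day 7, infants still in the NICU on day 7, outcomes counted from day 7. Since infants may be admitted at up to 14 days of age, say whether day 7 is age or day of stay.
3. For stay, model time to discharge home, with death as a competing event and escalation transfer as a separate competing event. Treating escalation transfer as uninformative censoring would be wrong if these infants are sicker than those who remain. State how convalescent transfer enters.
4. For mortality, add a sensitivity analysis of death or escalation transfer.

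The cost is plan wording and modest programming. Creatinine values and disposition codes are already collected, and the 48-hour and 7-day windows in Table 3 already require dated values. The landmark drops AKI after day 7 and infants who leave or die before it, which is why it should support the time-dependent analysis and not replace it.
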